### Assessing capacity and obtaining informed consent

Informed consent will be sought by a trained researcher using a combined informal
capacity assessment/consent process.^44^ Both
verbal and written information will be provided about the study, using a style and
format suitable for the participant group (ie, for varying levels of capacity). The
researcher will ask the potential participant to recount the study which will be
used, with the treating team views, to assess capacity to consent. For participants
judged to have capacity, consent will be sought for:conducting assessments as specified in the study information sheets;accessing health records for information relevant to outcomes and health
service use andrecording these data in secure study databases.

It will be made clear to participants that they are under no obligation to take part,
their usual care will not be affected by their decision and they can withdraw consent
without giving a reason. Once participants are enrolled in the study, they will be
given a sheet with contact details for the research team and instructions on what to
do if they wish to withdraw consent or require further information.

### Lack of capacity to consent

It is essential that this study recruits patients which reflect the target clinical
population. This means that we must recruit patients with delirium in the same
proportion as in the clinical population. We will seek consent/agreement from legal
proxies, consultees or other legal representatives. Where the potential participant
is deemed to lack capacity to consent, recruitment will proceed under the provisions
of the Mental Capacity Act, 2005 in England or Adults with Incapacity (Scotland) Act,
2000. The clinical team will be asked to identify an appropriate personal or
nominated consultee, guardian, welfare attorney or nearest relative.

Because of differing legal requirements in Scotland and England, the details of the
processes in each nation are given in online Supplementary appendix 1.

10.1136/bmjopen-2016-015572.supp1Supplementary Appendix 1

### Interventions to be measured

Assessments will be carried out by researchers fully trained in background
information on delirium, the features of delirium and each rating scale. Training is
carried out using written, video and bedside training until competence in all aspects
of the assessments is achieved.

### The 4 A’s Test

The 4AT (see www.the4AT.com) comprises four items. Item 1 concerns an observational
assessment of level of alertness. The next two items are brief cognitive tests: the
Abbreviated Mental Test–4 (AMT4) which asks the patient to state their age,
their date of birth, the current year and the place they are in, and attention
testing with Months Backwards, in which the patient is asked to state the months of
year in reverse order, starting with December. Only items 1–3 are done at the
bedside, and the typical duration is under 2 min. Item 4 concerns acute change
in mental status, a core diagnostic feature of delirium; this information is obtained
from the case notes or the general practitioner (GP) letter or from an
informant.

### Short CAM

The CAM is a diagnostic algorithm in which the tester rates the following four
features as positive or negative: (1) Acute Change and Fluctuating Course; (2)
Inattention; (3) Disorganised Thinking and (4) Altered Level of Consciousness. The
CAM scoring process requires that Features 1 and 2 are both positive; if they are
positive, then Features 3 and 4 are assessed and if one of Features 3 or 4 is
positive, then the whole CAM is positive. The tester scores the features by a
combination of interview with the patient, cognitive testing (the CAM requires that a
cognitive test is performed before the features are scored), examining the case notes
and seeking informant history if required. Note that the questionnaires used to
assess cognition are not specified by the CAM manual, though some suggested tests are
provided. Feature 1 is assessed by the same process as Item 4 in the 4AT. Feature 2
is assessed by the tester giving a positive or negative rating to the question,
‘Did the patient have difficulty focusing attention, for example, being easily
distractible or having difficulty keeping track of what was being said?’
Feature 3 is assessed by the tester giving a positive or negative rating to the
question, ‘Was the patient’s thinking disorganised or incoherent, such
as rambling or irrelevant conversation, unclear or illogical flow of ideas or
unpredictable switching from subject to subject?’ Feature 4 is similar to Item
1 in the 4AT. In this study, for the pre-CAM cognitive assessment, we will use a set
of questions covering the cognitive domains represented in the suggested tests in the
CAM manual, including Days of the Week Backwards, counting from 20 down to 1,
orientation questions, three-word recall and clockdrawing, as well as simple
orientation questions. All of these questions are used in routine clinical practice
at the bedside.

### Reference standard assessment

Reference standard assessment: this will be centred on the Delirium Rating
Scale-Revised-98 (DRS-R98),^45^ requiring
inspection of case notes, speaking to staff who know the patient or speaking to the
patient’s relatives or others who know them (with patient consent). As per the
instruction manual, the DRS-R98 will be supplemented by short neuropsychological
tests of attention and other domains, including Digit Span,^27^ the Observational Scale for Level of Arousal,^46^ the Richmond Agitation Sedation Scale^47^ and the DelApp objective attentional
assessment.^48^ We will also perform simple
orientation questions and record any formal prior diagnosis of dementia and
IQCODE^49^ scores. The DRS-R98 and supporting
tests will be used to inform a binary ascertainment of delirium based on DSM-IV
criteria. The final DSM-IV ascertainment of delirium will be based on a standardised
process with final verification by the chief investigator, blind to the 4AT or CAM
results. The panel of supporting tests, and the way the data are coded will be
designed such that the performance of the 4AT can also be evaluated against the DSM-5
criteria.^2^ The reference standard assessment
will take approximately 15–20 min.

### Ordering of assessments

All patients will undergo a reference standard assessment for delirium by the
researcher who conducted the capacity assessment and consenting process. A different
researcher will also ask each patient to undergo either the 4AT or the CAM. The
reason that the researcher doing the capacity assessment and consenting process must
also do the reference standard assessment is that the capacity and consenting process
provides information to the tester over and above the normal 4AT or CAM testing
process. This is not a concern for the reference standard assessment, which is aimed
at providing a thorough assessment so as to optimise diagnostic accuracy. The order
of these two assessments ((4AT or CAM assessment) and reference standard assessment)
will be randomly allocated immediately after consenting, as will the assignment to
either the 4AT or the CAM. Each patient will receive the reference standard
assessment by the same researcher who did the capacity and consenting process. The
4AT or CAM will be performed by a different researcher. When possible, the IQCODE
will then be administered to a person who knows the patient well (within
4 weeks of the patient joining the study).

### Randomisation procedure

The allocation sequence will be created using computer-generated random numbers.
Participants will be randomised in a 1:1 ratio to be assessed using the 4AT or CAM
experimental assessment. The order in which they receive the reference standard and
experimental assessment will also be randomised in a 1:1 ratio. Randomisation will be
stratified by study site with block allocation. The randomised allocations will be
concealed until they are assigned, as the randomisation system will be
web based and requires a personal login and password. Once randomisation has
been performed, neither the researchers nor the participant will be blinded to the
allocation as both will be aware of the assessments conducted and the order in which
they are performed.

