## Abstract

**Introduction:**

Delirium is a severe neuropsychiatric syndrome of rapid onset, commonly
precipitated by acute illness. It is common in older people in the emergency
department (ED) and acute hospital, but greatly under-recognised in these and
other settings. Delirium and other forms of cognitive impairment, particularly
dementia, commonly coexist. There is a need for a rapid delirium screening tool
that can be administered by a range of professional-level healthcare staff to
patients with sensory or functional impairments in a busy clinical environment,
which also incorporates general cognitive assessment. We developed the 4
’A’s Test (4AT) for this purpose. This study’s primary
objective is to validate the 4AT against a reference standard. Secondary
objectives include (1) comparing the 4AT with another widely used test (the
Confusion Assessment Method (CAM)); (2) determining if the 4AT is sensitive to
general cognitive impairment; (3) assessing if 4AT scores predict outcomes,
including (4) a health economic analysis.

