**Trial registration number:**

ISRCTN53388093;
Pre-results.

Strengths and limitations of this studyThe study protocol involved seeking a representative sample of older acute medical
patients in the emergency department and acute medical wards. A detailed,
structured reference standard with explicit and reproducible methods is used to
assess the features of delirium and reach a diagnosis.Two different rating scales, the 4 ‘A’s Test (4AT) and the Confusion
Assessment Method are being evaluated in similar groups of patients.Reference standard and index assessments were performed blinded to each other.A limitation of the study is that participants or legal proxies were required to
give consent and thus the sample was selected.

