## Discussion

This study was designed to validate the 4AT against a reference standard assessment, as
well as compare it with another commonly used test for assessment of delirium. Since the
initial study design, the 4AT has been widely adopted nationally and internationally.
The 4AT has been incorporated into routine practice in multiple international centres,
both in paper and electronic format, with many centres reporting 10 000 uses of
the tool. The website www.the4AT.com has had an increasing degree of traffic, and the 4AT has
been translated into multiple languages. The 4AT is also included in several national
guidelines and position statements internationally as a recommended tool and it has been
validated in other studies^38–42^ but it is still essential that it is further tested in a large
study. It is also essential to consider how well it identifies other types of cognitive
impairment, relates to future outcomes and its health economic impact.

In the initial design and implementation of the study, the main challenging aspects have
been: (1) considering both Scottish and English legal and ethical framework to ensure
that patients without capacity are included. Ethical approval for inclusion of these
patients was granted though recruitment of this patient group proved difficult from the
outset for several reasons. First, the narrow boundaries for the screening and
identification strategy. This was addressed in a subsequent protocol amendment to aim
for oversampling of patients at risk of developing delirium. Second, the availability of
an appropriate individual to provide consent on behalf of the participant (ie, a
personal or nominated consultee, guardian, welfare attorney or nearest relative). Third,
a reluctance to consent due to perceived burden on participant. Persuading relatives of
the value, importance and necessity of research even in clinically unwell patients
demands a particular skillset from researchers and involved perseverance and excellent
communication in order to achieve recruitment targets.

(2) Recruitment and training of staff, with some staff moving to different posts,
and new staff being recruited and requiring training; in each case, detailed training
supported by reading materials and practice sessions was provided.

We also acknowledge that it is possible that researcher bias may influence how the
different index assessments (4AT or CAM) were scored. We also acknowledge that given the

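### The researcher who makes the reference diagnosis knows which tool the patient was allocated to, so the reference threshold could differ between the 4AT and CAM arms

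*Protocol article*

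**What the plan says.** Under Ordering of assessments, the order of the two assessments "will be randomly allocated immediately after consenting, as will the assignment to" the 4AT or the CAM. Each patient then has the reference standard "assessment by the same researcher who did the capacity and consenting process", and a different researcher gives the index test.

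Under Randomisation procedure, the text says that, once this step has "been performed, neither the researchers nor the participant will be blinded to the" assignment. The reason given is that each of them will know which tests are carried out and in what sequence.

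Under Reference standard assessment, the DRS-R98 and supporting tests inform a yes/no DSM-IV diagnosis, reached by a standardised "process with final verification by the chief investigator, blind to the 4AT or CAM" results. Nothing is said there about allocation.

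The Strengths and limitations list states: "Reference standard and index assessments were performed blinded to each other". The Discussion adds a caveat: "We also acknowledge that it is possible that researcher bias may influence how the" two index tests were scored. It has no matching caveat for the reference standard.

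**The concern.** The 4AT and the CAM are given to different patients. Comparing their sensitivity and specificity is therefore fair only if the reference standard is applied in the same way in both arms. Randomisation balances the patients. It does not balance a diagnosis that is made after the allocation is known.

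The reference diagnosis is partly a judgement. The researcher weighs test scores, case notes and informant accounts, and can probe more or less hard and set the bar higher or lower. If knowing the tool changes either habit, the two arms are measured against slightly different yardsticks, and the confidence intervals will not show it. The Abstract says that the authors developed the 4AT, which makes protection of the reference standard more valuable, but the point does not depend on anyone's preference.

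The exposure is also avoidable. The index tester and the patient must know the tool. The reference researcher does not give the index test and needs to know only who goes first.

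**Working it through.** **1. Who knows what, and when.**

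| Step | Source section | Consequence |
|---|---|---|
| Tool and order allocated straight after consent | Ordering of assessments | Both fixed before any reference assessment |
| Consenting researcher does the reference standard | Ordering of assessments | Same person throughout |
| Researchers not blinded to allocation | Randomisation procedure | Reference researcher knows the tool, even when the reference assessment comes first |
| Different researcher does the index test | Ordering of assessments | Reference researcher has no need of the tool |
| Verification blind to index results | Reference standard assessment | Blinding to allocation unstated |

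**2. The plan's own precision figures.** The half-width is 1.96 × √(p(1−p)/n), with 67 reference-positive and 383 reference-negative patients per arm (Sample size calculation).
- Sensitivity at 0.9: 1.96 × √(0.09/67) = 0.072
- Specificity at 0.9: 1.96 × √(0.09/383) = 0.030

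Both agree with Table 1, as do its other rows. These figures serve only as a yardstick here.

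**3. Illustration of a threshold shift in one arm.** The inputs are assumptions: k = 3 to 7 patients change reference status, and a share q = 0.3 to 0.5 of them are index-positive. Starting sensitivity is 0.70 (the planning value) or 0.897 (the earlier Italian validation study, quoted under Rationale for the study), so true positives TP = 46.9 or 60.1.

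*Stricter threshold:* k positives become negative, and sensitivity = (TP − kq)/(67 − k).
- From 0.70: (46.9 − 1.5)/64 = 0.709 to (46.9 − 2.1)/60 = 0.747
- From 0.897: (60.1 − 1.5)/64 = 0.916 to (60.1 − 2.1)/60 = 0.967

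*Laxer threshold:* k negatives become positive, and sensitivity = (TP + kq)/(67 + k).
- From 0.70: (46.9 + 1.5)/70 = 0.691 to (46.9 + 2.1)/74 = 0.662
- From 0.897: (60.1 + 1.5)/70 = 0.880 to (60.1 + 2.1)/74 = 0.841

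Sensitivity therefore moves by about 0.01 to 0.07 upwards or 0.01 to 0.06 downwards. Specificity moves by less than 0.01, because 383 patients absorb the change.

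**4. Could the drift be seen afterwards?** Compare reference-positive rates of 67/450 = 14.9% and 62/450 = 13.8% (5 cases) or 60/450 = 13.3% (7 cases), using the two-proportion normal formula at two-sided 5%. For 5 cases, the standard error of the difference is √(2 × 0.1433 × 0.8567/450) = 0.0234. Power is Φ((0.0111 − 1.96 × 0.0234)/0.0234), about 7%. For 7 cases it is about 10%. A drift of this size would usually pass unnoticed.

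**The case against.** The strongest reply is that the study already blinds what matters most. A different researcher does the index test, the two assessments are blinded to each other, and verification is blind to index results. The reference standard is structured and includes objective attention tests. This stands, and it limits the mechanism. A reader might infer that an assessor who knows the arm could move discordant patients into agreement and so create a 4AT advantage. The documents do not support that: picking out discordant patients requires the index result, which is concealed. The overlap between the reference tests and the 4AT items may let an assessor guess a likely result, but the documents give no figure for how well.

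A reader might also infer that the chief investigator verifies with the arm in view. The text does not say so. It is silent, and the contents of the verification file may be set out in the full protocol.

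Nor is the statement in the Strengths and limitations list contradicted, since blinding to each other's findings can coexist with knowledge of the allocation.

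Finally, the comparison most exposed is a secondary objective, and the shifts illustrated are no larger than the ±0.072 half-width for sensitivity at 0.9 and well below the 0.224 difference that the study is powered to detect. That is fair, and it keeps the point modest. It does not remove it, because bias is not reduced by sampling more patients and the exposure serves no purpose.

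**Conclusion.** The point holds as a limited design weakness. As written, the reference researcher knows the tool in every patient before making the diagnosis, without needing to, and the article does not state that verification is blind to allocation. Threshold or effort could therefore differ by arm.

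The direction is uncertain: a stricter reference in one arm raises that arm's apparent sensitivity and a laxer one lowers it. The size cannot be derived from the documents; the 0.01 to 0.07 range rests wholly on the assumed reclassification of 3 to 7 patients. The main exposure is the 4AT versus CAM comparison. The primary estimate of 4AT accuracy is affected only if the threshold moves within the 4AT arm. The Discussion's caveat on researcher bias covers index-test scoring and leaves this route unmentioned.

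**What to change.** - For patients still to be recruited, have the web randomisation system show the consenting/reference researcher only the order. Release the tool to that researcher once the reference form is complete.
- For all patients, do the final verification from files stripped of tool and order. State in the protocol that it is blind to allocation as well as to 4AT or CAM results.
- Report by arm the proportion reference-positive and the number and direction of diagnoses changed at verification. Treat these as descriptive: with power of about 7 to 10% for a drift of 5 to 7 cases, similar rates would not show that there was no drift.
- If masking is not adopted, state in the limitations that the reference assessor knew the allocation.

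The cost is a change to the randomisation display and to the verification extract. No extra staff are needed, since a second researcher already gives the index test, and the sample size is unchanged. Some unmasking on the ward must be expected, mainly in patients who have the index test first. The display change will reach few patients if recruitment is near its end (completion was planned for December 2016), whereas masked verification and reporting by arm do not depend on further recruitment.

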### Outcome measurements (what, when, how)

Note that the outcome measurements for the primary study (the reference standard) are
performed at almost the same time as the 4AT and CAM. The only subsequent data
collection is capturing clinical outcomes at 12 weeks. This will be achieved
through searching electronic patient records, telephone calls with participants or
face-to-face interviews if still in hospital. The information gleaned at the
12-week point will at times be generalised due to participant recall or availability
of full electronic records.

(1) Primary outcome measure:

Diagnostic accuracy of the 4AT versus the reference standard delirium diagnosisSecondary outcome measures:4AT versus CAM in relation to reference standard delirium diagnosis.Performance of 4AT cognitive test items (AMT4 and Months Backwards) in
detecting longer term cognitive impairment as detected by the
IQCODE.4AT total scores as a predictor of the following clinical outcomes as
determined at 12 weeks post-test: length of stay, falls,
institutionalisation (as assessed by proportion of patients newly admitted
to care homes or awaiting care homes at that time) and mortality.Performance of individual items of the 4AT in relation to reference standard
delirium diagnosis.We will assess the 4AT total score as a measure of delirium severity.The primary output from the health economic analysis will be a comparison of
the service delivery costs associated with the diagnostic accuracy of
alternative (4AT vs CAM vs reference standard) triage tools for
delirium.

### Coding and recording assessments

The experimental assessments of delirium will be the 4AT and the CAM. The 4AT has a
total possible score of 12: items (1) and (4) can score 0 or 4 and items (2)
and (3) can score 0, 1 or 2.^12^ 4AT data will
be used for the primary objective as a binary outcome, with 0–3 scores giving
a ‘no delirium’ classification, and 4–12 scores giving a
‘delirium’ classification; for the secondary objectives, continuous
scoring, from 0 to 12, will be studied as a possible severity indicator, and scores
of 1–3 (indicating cognitive impairment but not delirium) can be studied
against other assessments of chronic cognitive impairment. The CAM will
be scored as delirium present or absent according to the algorithm. The 4AT,
CAM scoring and reference standard scoring will be recorded on a paper Case Report
Form.

Patient resource use will be derived from medical records, including the
‘TrakCare’ (InterSystems Corporation, Cambridge, Massachusetts, USA)
electronic patient record system, where available, as well as via patient or carer
self-report. The self-report resource-use questionnaire will include questions
regarding inpatient health and social care utilisation with a maximum recall period
of 16 weeks. The self-report resource-use questionnaire will be developed
specifically for the study for use by patient or proxy respondent using guidance from
the Database of Instruments for Resource Use Measurement.^50^ Administration of the questionnaire will be conducted at
12 weeks by one of the researchers in the study team, face to face where
patients are still hospitalised or via telephone. Data from the questionnaire will be
recorded on a paper Case Report Form.

The data on all the Case Report Forms will be transcribed into a secure database by
the researchers or a suitably qualified member of the research team. This will be
conducted using Edinburgh Clinical Trials Unit Standard Operating Procedures. Quality
checking will be performed in 10% of Case Report Forms.

